#### 2.6.3. Telephone Coaching (Coaching Group)

Participants in the coaching group receive twelve biweekly telephone coaching sessions. Coaching sessions last 15–20 minutes during the course of the intervention and 30–40 minutes in the first two sessions. Participants are called by the same coach for the entire intervention period. If the biweekly rhythm is interrupted (e.g., due to vacations) or if participants miss a call, coaches can reschedule the session. Occasional variation of the biweekly rhythm between 1 and 3 weeks between each coaching session is considered normal. After each call the coaching session is summarized in a few sentences on the “note board” of the participant. Participants and coaches can leave remarks on the note board but it does not serve as a chat function.

The coaching refers to an interactive discussion between participant and coach. In accordance with the definition of health coaching by Olsen [11], the sessions are goal-oriented, client-centered, and focused on PA. Questions on nutrition or other health-related concerns as well as unrelated topics are not answered in detail. Coaches encourage their participants to build autonomy, self-confidence and self-efficacy and to gain knowledge and experiences concerning the benefits of PA. 

All coaching sessions contain the elaboration of BCTs and advice on training concepts. The scope of each specific coaching session is stated in the written guidelines. During the first sessions, coaches focus on the development of a functional relationship and deliver information on the procedure of the coaching. Additionally, coaches start to encourage participants to set goals and to plan their physical activities. Established activity plans are inserted in the personal profile on the homepage and visible for participant and coach. With support of the coach, participants proceed to the following session by establishing coping strategies to overcome personal barriers. All main BCTs and additional BCTs are delivered as required in the 12 sessions. Based on the self-monitoring data which is visible on the profile and based on the discussion during the coaching sessions, participants receive feedback concerning their behavior change towards a physically active lifestyle. Towards the end of the 12 sessions, coaches focus on the maintenance of PA levels.

#### 2.6.4. Telephone Coaching and SMS Prompting (Coaching and SMS Group)

Participants allocated to the coaching and SMS group receive the same telephone coaching as the coaching group. Additionally, participants in this group receive four SMS prompts during each two-week period (48 in total). The SMS are written, sent, and timed by the corresponding coach through an online platform. SMSs have the consignor of Movingcall and it is not possible to respond. Participants are asked if they have a preferred time (morning, noon, afternoon, evening) to receive the prompts. Within this time the SMSs are sent at variable time points. During each two-week period participants receive one SMS relating to PA knowledge, one relating to discussed BCTs, one containing a reminder, and one that consists of a feedback on documented physical activities (examples in Table 3). The language style and length of the SMSs are standardized and all SMSs are collected and saved.

#### 2.6.5. Intervention Provider

The coaching sessions are held by 28 trained sport science and psychology students. The training of the coaches consists of ten lectures and practical exercise for telephone coaching. Coaches are provided with an online handbook on BCTs and written guidelines. The following topics are included in the training: (1) The application of BCTs and the theory of behavior change; (2) An autonomy-supportive and client-centered coaching style; (3) Knowledge based on exercise and movement science to advice previously inactive adults; (4) The tailoring procedure; (5) Standardization of the intervention delivery (including written recommendation and SMSs); and (6) Data collection and documentation of the intervention. Each coach takes part in a one-hour know-how-check prior to the first coaching session, to ensure the coaching skills are sufficient. During the intervention delivery, current challenges in coaching situations are discussed and above listed topics are deepened in biweekly team meetings. 

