#### 2.6.7. Minimal Intervention (Control Group)

Participants allocated to the minimal intervention group receive a single written recommendation about health-enhancing PA at the beginning of the intervention. The recommendation is tailored individually and covers information on all main BCTs. An exemplary PA plan and an explanation on how to adapt the plan is included. Participants in this group are asked to follow the recommendation, to self-monitor and plan their PA within their profile on the homepage and by doing so increase PA gradually during the intervention period. Recommendations are written by the coaches within a predefined template. Participants receive their recommendation as a PDF by e-mail and it is inserted on the note board within the personal profile. Participants in the minimal intervention group only have contact with the study team during data assessments.

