#### 2.7.2. ActiGraph Data

PA of 1 week is objectively assessed with the ActiGraph wGT3X-BT. The triaxial accelerometer records intensity and duration of accelerations and converts the signals to “activity counts” [55]. Participants receive the device by post at the beginning of the pre-, post-, and follow-up assessment period. All participants are requested to wear the ActiGraph on the non-dominant wrist for 7 to 10 consecutive days and nights. Hip-worn accelerometers are regarded as superior for predicting locomotion and estimating energy expenditure [73]. However, estimates of moderate and vigorous PA of wrist- and hip-worn accelerometers are comparable [74]. While hip-worn accelerometers are today’s standard, wrist-worn accelerometers have demonstrated higher wear-time compliance [74,75]. Wrist-worn assessment is therefore considered more feasible for the remote setting. 

Each participant is called by the allocated coach to explain how to handle the ActiGraph and the procedures of the test period. Participants are asked to wear the device until the SIMPAQ interview that is arranged after the requested wear time. The ActiGraph should be ignored and only removed when swimming or in a sauna. Non-wear periods are reported on a sheet enclosed in the mail. A prepaid envelope is attached for returning the ActiGraph along with the sheet.

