### 2.8. Data Processing and Statistical Analysis

ActiGraph data are analyzed using the ActiLife software (Version 6.13.3, ActiGraph, Pensacola, USA). Daily minutes of moderate-to-vigorous physical activity (MVPA) are computed after declaring sleep and non-wear time. Currently there are no widely used and validated cut-off-values to classify MVPA for adults’ activity count of wrist-worn ActiGraph data. The cut-off values are therefore chosen on the basis of existing explorative analysis [77] and their comparison to cut-off points for children [78]. According to Kamada et al. [77] activity counts per minute are classified as sedentary activity 0–1999, light activity 2000–8249, and MVPA > 8249. The option “worn on the wrist” provided by the ActiLife software is not selected given its systematic underestimation of energy expenditure [79]. Sleep is determined using the Cole–Kripke algorithm [80]. Non-wear time is calculated according to Troiano [81]. Physical activities listed on the non-wear sheet (e.g., swimming) are added as moderate activities. In order to be analyzed, participants need to have a non-wear time of less than 10% [82]. At least four weekdays and one weekend day are required [55]. The first day of wear-time is not included. For further analysis, the mean of MVPA per day of all assessed valid days is computed.

All statistical analysis will be conducted as intention-to-treat. Group differences in primary and secondary outcomes will be calculated using linear mixed models. Linear mixed models will include intervention group, time, group × time interaction, and baseline measures as fixed effects and subjects as random effects. Statistical analysis will be conducted using the statistical software STATA (StataCorp, College Station, USA). Effect sizes for pre-post change scores and the corresponding confidence intervals will be provided [83,84].

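### The mixed model has no coach term although 28 coaches each treat about 7 coached participants, so the standard errors of the coaching contrasts may be mis-stated, in a direction the article does not settle

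*Protocol article*

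**What the plan says.** On delivery, Section 2.6.5 of the protocol article states: "The coaching sessions are held by 28 trained sport science and psychology students". Section 2.6.3 adds: "Participants are called by the same coach for the entire intervention period". In the third arm the same coach also handles the prompts (Section 2.6.4): "The SMS are written, sent, and timed by the corresponding coach through an online platform".

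Coaches also have some part in the control arm. Section 2.6.7 states: "Recommendations are written by the coaches within a predefined template". Section 2.7.2, which covers all arms, states: "Each participant is called by the allocated coach to explain how to handle the ActiGraph and the procedures of the test period".

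On analysis, Section 2.8 states: "Linear mixed models will include intervention group, time, group × time interaction, and baseline measures as fixed effects and subjects as random effects". No coach term is named. The sample size paragraph in Section 2.2 describes an ANCOVA adjusted for baseline and mentions no clustering. The article gives no coach ICC and no caseload per coach, and does not say whether a coach works in one coaching arm or in both.

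**The concern.** A participant receives 12 calls from one person, who tailors the content, chooses among 25 optional techniques and, in one arm, composes the 48 text messages. Participants of the same coach may therefore have outcomes more alike than participants of different coaches. A subject random effect handles repeated measurements on one person. It does nothing for correlation between people who share a coach, so the coach variance is absorbed into the between-subject variance and participants are treated as independent.

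At stake is the precision claimed for the two hypotheses in Section 3: that both coaching arms outperform the minimal intervention, and that coaching with prompting outperforms coaching alone. The second depends most on the unstated coach-to-arm layout.

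**Working it through.** **Inputs.** There are 28 coaches (Section 2.6.5) and 288 randomised participants in three arms (Abstract). The allocation ratio is not given; 1:1:1 is assumed, so n = 96 per arm and 192 coached. The ICC is not given; 0.01, 0.02, 0.05 and 0.10 are assumed. The plan has no design effect or ICC of its own to reproduce.

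**Caseload.** 192/28 = 6.86 coached participants per coach, or 96/28 = 3.43 per coach in each coaching arm if coaches serve both. If each coach serves one coaching arm (14 per arm), it is 96/14 = 6.86. Counting controls as well, 288/28 = 10.3.

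**Variance of each contrast.** Set the total variance to 1 in every arm and the coach variance to the ICC. The model without a coach term uses 2/n for a difference of two arm means. A coached arm mean has variance DE/n, where DE = 1 + (m − 1) × ICC and m is the number per coach within that arm.

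- *(a) Coaches serve both coaching arms, m = 3.43.* Coaching versus control: true variance (DE + 1)/n, so the ratio of true to modelled standard error is √((DE + 1)/2). At ICC 0.05, DE = 1 + 2.43 × 0.05 = 1.12 and the ratio is √(2.12/2) = 1.030. For SMS versus coaching a coach effect common to both arms cancels, leaving 2(1 − ICC)/n and a ratio of √(1 − ICC) = 0.975.
- *(b) Each coach in one coaching arm, m = 6.86.* At ICC 0.05, DE = 1 + 5.86 × 0.05 = 1.29. Coaching versus control: √(2.29/2) = 1.071. SMS versus coaching: √1.29 = 1.137.
- *(c) Coach effect shared equally by all three arms.* It cancels in every contrast, so each ratio is √(1 − ICC).

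**True standard error divided by modelled standard error**

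| ICC | (a) coaching v control | (a) SMS v coaching | (b) coaching v control | (b) SMS v coaching | (c) any contrast |
|---|---|---|---|---|---|
| 0 | 1.000 | 1.000 | 1.000 | 1.000 | 1.000 |
| 0.01 | 1.006 | 0.995 | 1.015 | 1.029 | 0.995 |
| 0.02 | 1.012 | 0.990 | 1.029 | 1.057 | 0.990 |
| 0.05 | 1.030 | 0.975 | 1.071 | 1.137 | 0.975 |
| 0.10 | 1.059 | 0.949 | 1.137 | 1.259 | 0.949 |

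**Type I error at nominal two-sided 5%**, from 2 × (1 − Φ(1.96/ratio)):

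- ICC 0.05: 5.7% and 4.4% in (a), 6.7% and 8.5% in (b), for coaching versus control and SMS versus coaching respectively.
- ICC 0.10: 6.4% and 3.9% in (a), 8.5% and 12.0% in (b).

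Simulation with 20,000 trials per scenario agrees. At ICC 0.05 it gives 5.3% and 4.3% in (a) and 6.8% and 8.5% in (b). At ICC 0.10 it gives 6.4% and 3.8% in (a) and 8.4% and 12.2% in (b).

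**Sensitivity.** With 242 analysed, the caseload falls to 161.3/28 = 5.76. At ICC 0.10 the ratios become 1.046 and 0.949 in (a), and 1.113 and 1.215 in (b).

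**A limit of layout (a).** The cancellation for SMS versus coaching assumes that a coach has the same effect in both arms. Split the coach variance into a common part τ and a coach-by-arm part ω. The variance factor is then (1 − τ − ω) + 3.43ω = 1 − τ + 2.43ω, which exceeds 1 once 2.43ω > τ.

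**The case against.** A reader might infer that the planned standard errors are simply wrong, or that the intervals for coaching versus control are too narrow. The documents do not support either statement. Both need a coach ICC above 0 and a known layout, and the article gives neither. At ICC 0 there is no error.

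A reader might also take layout (b), with its 8.5% and 12.0%, as the headline. The text leans the other way. Coach training covers the written recommendation and the SMSs as well as the calls (Section 2.6.5). No separate pool of coaches is described for the SMS arm. An allocated coach phones each participant about the test period (Section 2.7.2), which includes the pre-test, while Section 2.4 says the study team did not know the allocation before the intervention started. Coaches attached to participants before the arm was known are hard to square with arm-specific coaches. This is inference, not proof, but it makes (a) more plausible than (b).

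Two further points count against a large effect. The lectures, handbook, written guidelines, skills check and biweekly meetings in Section 2.6.5 should limit differences between coaches. Coaches also have some contact with controls, so a fully partially nested picture is not exact. That contact is one templated document and calls around assessments, set against 12 coaching sessions, so an equal coach effect in all three arms is the least plausible layout. It cannot be excluded from the text.

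Finally, the article is condensed, and an unseen analysis plan could add terms. This defence is weak here, because Section 2.8 names the fixed and random effects and lists only subjects as random.

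What stands is that the size is probably small and the direction open. The clustering and the missing term remain.

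**Conclusion.** The point holds in a conditional form. The stated model ignores clustering by coach, with about 7 coached participants per coach, so it fixes the coach ICC at zero without checking it. If the ICC is above 0, the standard errors of the coaching contrasts are mis-stated.

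Under the more plausible layout, coaching versus control is mildly anti-conservative, and SMS versus coaching is conservative unless coach effects differ appreciably between the two arms. Confining coaches to one coaching arm would make both contrasts anti-conservative, most of all SMS versus coaching. An effect shared equally by all arms would make every contrast conservative.

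These figures rest on 1:1:1 allocation, equal caseloads, equal total variance in the arms, and an assumed ICC range. The correction is worth making because the layout is unstated, the contrast most sensitive to it is one of the trial's hypotheses, and the remedy is cheap.

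**What to change.** 1. State how coaches were allocated to arms: one coaching arm, both, or all three.
2. Add a coach random effect that matches this. It should act in the two coaching arms, with a coach-by-arm term if coaches serve both. Treat controls as singletons only if their limited coach contact is judged negligible.
3. Use small-sample degrees of freedom (Kenward-Roger or Satterthwaite, both available in Stata's mixed command), since there are only 28 coaches.
4. Report the estimated coach ICC.
5. If the primary model is to stay as written, pre-specify the model with the coach effect as a sensitivity analysis.

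The cost is a few lines of analysis text and, under layouts (a) and (b), slightly wider intervals for coaching versus control. No new data collection is needed provided that coach identity is held for each participant. This is likely, since each coach has access to the corresponding participant's profile (Section 2.6.2) and documents each session (Section 2.6.6), but the article does not state it.

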#### 2.6.6. Intervention Documentation and Assessment of Adherence

Applied BCTs are documented and coded by the coaches after each coaching session. In addition, the duration, date and time of each session is recorded. 

The adherence of participants to the intervention is assessed in two ways. First, the engagement of participants is assessed based on their personal profile. The amount of active edits of each participant within the personal profile is recorded (e.g., entering a planned PA). Second, the completeness of intervention delivery is assessed by documenting date, duration and number of attended coaching sessions. Thereby the subcategories “standard”, “not standard”, “non-usage attrition”, and “dropout” are distinguished [54]. A total of 12 coaching sessions with up to two interruptions of maximum four weeks between two coaching sessions and an overall intervention duration of 22 (norm) to 26 weeks are considered as standard. Participants who stop the coaching (non-usage attrition) are asked for possible reasons and asked to still participate in the post and follow-up-tests. Individuals lost to post and follow-up-tests are considered as dropouts. 

#### 2.6.7. Minimal Intervention (Control Group)

Participants allocated to the minimal intervention group receive a single written recommendation about health-enhancing PA at the beginning of the intervention. The recommendation is tailored individually and covers information on all main BCTs. An exemplary PA plan and an explanation on how to adapt the plan is included. Participants in this group are asked to follow the recommendation, to self-monitor and plan their PA within their profile on the homepage and by doing so increase PA gradually during the intervention period. Recommendations are written by the coaches within a predefined template. Participants receive their recommendation as a PDF by e-mail and it is inserted on the note board within the personal profile. Participants in the minimal intervention group only have contact with the study team during data assessments.

### 2.7. Assessment of Primary and Secondary Outcomes

The assessment of primary and secondary outcomes is conducted without on-site presence of participants. Self-reported and objectively assessed PA level of one week, theoretical domains of PA as well as health and wellbeing-related variables are assessed in the pre, post and follow-up tests. After 3 months of intervention all participants are asked to answer a feedback questionnaire. Personal data and socio-demographic information are assessed during the inclusion procedure. Measures of all test periods are displayed in Table 4.

#### 2.7.1. Self-Reported Physical Activity

A structured telephone interview is carried out to assess participants’ self-reported PA. This interview follows the questions described in the SIMPAQ (Simple Physical Activity Questionnaire) [40]. In the present study, self-reported PA serves as the primary outcome. The SIMPAQ refers to PA during the previous 7 days. Furthermore, the structured interview asks for the time spent in bed and the time spent with the activities “sitting or lying”, “standing”, “walking”, and “other activities” (e.g., house work, gardening) for one of the usual days of the previous week. The duration and intensity of athletic training and recreational physical activities are assessed separately for each day. SIMPAQ was validated with university students by Schilling et al. [70] and has shown a moderate to strong correlation to accelerometer data and to established self-report questionnaires (Seven-Day Physical Activity Recall [71] and the short form of the International Physical Activity Questionnaire [72]). Compared to other self-report questionnaires the SIMPAQ is less time consuming [70]. 

In the present study, the original version of the SIMPAQ interview is extended to assess moderate or vigorous activities in everyday life. The intensity of the time spent walking and the time spent with other activities is specified by the question “how much of this time did you walk/move with an intensity that leaves you slightly out of breath?” Additional questions are added to the interview to assess: (1) If the last week is considered “a normal week”; (2) Illnesses and injuries during the last week; (3) Illnesses and injuries during the past 6 months including days of occupational absences; (4) Regular medication; and (5) Body weight including the time point and the location of weighing. In the post and follow-up tests two more questions are added to assess: (6) Other health-related behavior change attempts (e.g., stop smoking); and (7) The attendance to other services that support PA-related behavior changes (e.g., physiotherapy).

Interviews are conducted by specifically trained members of the study team. They are never conducted by the coach of a participant and interviewers are unaware of the group allocation.

#### 2.7.2. ActiGraph Data

PA of 1 week is objectively assessed with the ActiGraph wGT3X-BT. The triaxial accelerometer records intensity and duration of accelerations and converts the signals to “activity counts” [55]. Participants receive the device by post at the beginning of the pre-, post-, and follow-up assessment period. All participants are requested to wear the ActiGraph on the non-dominant wrist for 7 to 10 consecutive days and nights. Hip-worn accelerometers are regarded as superior for predicting locomotion and estimating energy expenditure [73]. However, estimates of moderate and vigorous PA of wrist- and hip-worn accelerometers are comparable [74]. While hip-worn accelerometers are today’s standard, wrist-worn accelerometers have demonstrated higher wear-time compliance [74,75]. Wrist-worn assessment is therefore considered more feasible for the remote setting. 

Each participant is called by the allocated coach to explain how to handle the ActiGraph and the procedures of the test period. Participants are asked to wear the device until the SIMPAQ interview that is arranged after the requested wear time. The ActiGraph should be ignored and only removed when swimming or in a sauna. Non-wear periods are reported on a sheet enclosed in the mail. A prepaid envelope is attached for returning the ActiGraph along with the sheet.

#### 2.7.3. Psychosocial Determinants of PA and other Measures

Online questionnaires are used to assess additional secondary outcomes and information needed for individual tailoring. Questionnaires are programmed within the interactive homepage. A link to answer the questionnaires is sent to the participant by e-mail. 

Applied instruments have previously been used in empirical research in German speaking countries. Except for self-composed items, acceptable validity and reliability have been demonstrated in previous studies (references listed below).

The following measures are assessed in the pre- post- and follow-up test-periods.
**Intention**: Motivational readiness for PA-related behavior change is assessed according to the stages of change of the Transtheoretical Model [56,76]. Participants select one out of five answers to the question “Are you regularly physically active, this means at least 20 minutes on 3 days of the week?”, e.g., “No, but I intend to become more physically active in the next 6 months”. A single item to measure the strength of intention is added. Participants quantify their intention to be regularly physically active on a scale from zero (no intention) to five (very strong intention) [57,63].**Action planning** is measured by five items [61]. Participants are asked if they defined when, where, how, how often, and with whom they plan to exercise. For example “I have made a detailed plan regarding when to exercise”. Answers are given on a Likert-scale from one (not true) to four (completely true).**Outcome expectations** regarding regular PA are assessed with 16 items validated by Fuchs [59]. Participants are asked to rate their expectations towards specific outcomes on a Likert-scale ranging from one (not true) to four (completely true). For example “If I were physically active on a regular basis, I would lose weight”.**Self-efficacy** is assessed consistently with Fuchs [60] by three items. The confidence to begin, to maintain and to restart regular PA is measured on a six-point Likert-scale from one (No confidence) to four (100% confidence). For example, “I am confident that I could start with new physical activity”.**Perceived barriers:** Participants are presented 19 potential barriers (e.g., “being tired”) and asked to indicate how strong each one prevented PA on a Likert-scale from one (not at all) to four (very much) [46]. **Coping strategies** on barriers are measured by five items applied and validated by Sniehotta et al. [58]. For example “I have made a detailed plan regarding what to do if something interferes with my plans”. Responses are given on a four-point Likert-scale from one (not true) to four (completely true).**Social support** is assessed by seven items that rate the confidence for support of the social environment on a four-point Likert-scale from one (never) to four (always) [62]. For example, “I am confident that people of my social environment will be physically active with me”.**Self-concordance** is measured by four items on the self-concordance scale. The scale was composed and validated by Seelig and Fuchs [63]. Participants are asked to rate their internal/external motivation on a Likert-scale ranging from one (completely false) to four (completely true). For example, “If I am physically active within the next weeks and months, this is because other people say I should”.**Knowledge about health enhancing PA and fitness rating:** Participants are asked to rate their fitness level (on a scale from one to ten, one item) [64] and their level of health-enhancing PA (“Do you think you are sufficiently active for your health? Yes/No”, one item) [65]. Knowledge of general PA recommendations are assessed by two items previously used by Gerber et al. [66].**Perceived stress-related exhaustion symptoms** are measured by the validated Shirom–Melamed Burnout Measure (SMBM) [67]. Three subscales (physical fatigue, emotional exhaustion and cognitive weariness) are assessed within 14 items. **Health-related quality of life:** The Short–Form 12 Questionnaire (SF-12) is used to assess health-related quality of life [68,69]. The questionnaire includes 12 items on general physical health status and mental health distress. The questionnaire’s validity and reliability has been demonstrated by Craig et al. [36].

Two questionnaires are used to tailor the intervention content and are only applied in the pre-test. One questionnaire consists of family structure, living situation and workload in four self-compiled items. The other instrument assesses health restrictions, experience in PA and personal goals.

After 3 months each participant is invited to provide feedback on aspects of the intervention. The self-compiled questionnaire measures general satisfaction with the program, goal achievement, motivation to proceed and participant’s opinion on possible program extensions (e.g., interaction with other participants). Participants are asked to rate the usability of the personal profile, to evaluate the value of BCT-based advice and to name the most important recommendation for them personally. The control group is asked to rate the written recommendation. In the coaching and the coaching and SMS group the quality of the relationship between participant and coach is assessed. In the coaching and SMS group, it is evaluated whether the SMSs are perceived as beneficial and what topic is considered most motivating. Questions specific to group allocation are asked a second time in the post-test.

